# Early treatment of Atrial fibrillation for Stroke prevention Trial in acute STROKE (EAST-STROKE): protocol for an international investigator-initiated, prospective, randomised, open, blinded endpoint assessment (PROBE) interventional multi-centre trial

**DOI:** 10.1093/esj/aakag022

**Published:** 2026-05-19

**Keywords:** acute ischaemic stroke, atrial fibrillation, rhythm-control therapy, secondary stroke prevention

## Abstract

**Background:**

Acute ischaemic stroke patients with atrial fibrillation (AF) are at high risk of suffering a recurrent stroke or other cardiovascular complications. It is uncertain whether early rhythm-control therapy is effective and safe in preventing recurrent strokes and cardiovascular complications in these patients.

**Study design:**

Early treatment of Atrial fibrillation for Stroke prevention Trial in acute STROKE (EAST-STROKE) is an international investigator-initiated, prospective, randomised, open, blinded endpoint assessment (PROBE) interventional multi-centre trial. Patients with acute ischaemic stroke and AF will be randomised within 4 weeks of stroke (1:1) to receive either early rhythm control and usual care or usual care alone. Usual care includes oral anticoagulation, rate control and treatment of cardiovascular conditions. Early rhythm control additionally comprises treatment with antiarrhythmic drugs, AF ablation or cardioversion. A minimum of 1746 participants will be randomised to observe 351 events. The adaptive design includes one interim analysis with sample size re-estimation after 50% of events.

**Study endpoints:**

The primary outcome is a composite of first recurrent ischaemic stroke, haemorrhagic stroke, unclassified stroke, cardiovascular death or hospitalisation due to worsening of heart failure or due to acute coronary syndrome, analysed as time to the first occurrence. Secondary outcomes include individual components of the primary outcome, functional status and patient-reported outcome measures. Safety outcomes comprise all-cause mortality and adverse events. Patients will be followed-up until the end of the trial with a minimum follow-up period of 24 months and an expected mean follow-up period of 42 months.

**Summary:**

EAST-STROKE will determine whether early rhythm-control therapy in addition to usual care is effective and safe in patients with acute ischaemic stroke and AF.

**Trial registration:**

ClinicalTrials.gov Identifier: NCT05293080; EUCT-No.: 2025-521260-35-00.

## Introduction and rationale

Recurrent stroke is a major public health concern, affecting up to 25% of patients with ischaemic stroke within 5 years.^1^ Atrial fibrillation (AF) significantly increases stroke risk despite oral anticoagulation (OAC), leaving patients vulnerable to recurrent, often severe strokes.^2,3^ Moreover, AF is also associated with an increased risk of other major cardiovascular events such as myocardial infarction and heart failure.^4–7^

Historically, the risk of stroke was thought to be similar regardless of AF burden, and secondary stroke prevention focused not on AF itself but rather on preventing AF-associated thromboembolism via OAC. However, recent data point towards the role of AF burden, with lower stroke risk in patients with paroxysmal AF compared to chronic AF.^8^ Previous rhythm-control trials failed to show a stroke prevention benefit, likely due to patient selection, suboptimal rhythm-control rates and discontinuation of anticoagulation after restoration of sinus rhythm. The more recent Early Treatment of Atrial Fibrillation for Stroke Prevention Trial (EAST-AFNET 4) demonstrated that early rhythm control reduces stroke, cardiovascular death and hospitalisations in patients with AF and increased cardiovascular risk.^9^

The efficacy and safety of early rhythm control in patients with AF and acute ischaemic stroke have not yet been evaluated in an adequately powered outcome trial. The RAFAS (Risk and benefits of urgent rhythm control of Atrial Fibrillation in patients with acute Stroke) trial, which randomised 300 patients with acute ischaemic stroke and AF, suggested a reduction in recurrent stroke at 12 months with early rhythm-control therapy. However, its findings are limited by the small sample size and low number of events.^10^ A subgroup analysis from the EAST-AFNET 4 trial showed a strong effect of early rhythm control in patients with a history of stroke compared to those without, but EAST-AFNET 4 did not include patients with acute stroke. Large observational studies further support the potential benefit of early rhythm control in patients with AF and ischaemic stroke.^11^

Despite these findings, substantial uncertainty remains, as rhythm-control therapy carries potential risks that may be aggravated after an acute stroke, particularly in elderly and frail patients, highlighting the need for systematic safety evaluation before broader clinical adoption. An international survey underscored this clinical equipoise, with 80% of centres rarely using rhythm-control therapy in patients with acute ischaemic stroke and AF and 90% expressing willingness to enroll patients in a randomised trial.^12^ These findings were corroborated by a Canadian survey, in which only a minority of respondents reported offering treatments to restore sinus rhythm in patients with acute stroke and AF, whereas the vast majority (84%) indicated they would be willing to randomise patients in a clinical trial of early rhythm control after acute ischaemic stroke.^13,14^

Although rhythm-control therapies are associated with recognised risks, these are well characterised and often manageable. In EAST-AFNET 4, over a median follow-up of 5.1 years per patient, serious adverse events related to rhythm-control therapy occurred in 4.9% of patients assigned to early rhythm control.^9^ In particular, ventricular proarrhythmia with antiarrhythmic drugs can often be avoided by appropriate patient selection and electrocardiogram (ECG) monitoring.

Taken together, existing evidence suggests that early rhythm-control therapy may provide meaningful clinical benefit with acceptable safety. Therefore, the Early treatment of Atrial fibrillation for Stroke prevention Trial in acute STROKE (EAST-STROKE) aims to evaluate the efficacy and safety of early rhythm control in preventing recurrent stroke and major cardiovascular events in patients with AF and acute ischaemic stroke. Secondary objectives include assessing health-related quality of life, functional outcomes and cost-effectiveness.

## Methods

### Study design

EAST-STROKE is an international investigator-initiated, prospective, randomised (1:1), open, blinded endpoint assessment (PROBE) parallel-group interventional multi-centre trial to test whether an early, comprehensive, rhythm-control therapy in addition to usual care can reduce the rate of adverse cardiovascular outcomes in patients with acute ischaemic stroke and AF compared to usual care alone. Because it is addressing a novel process of care, it is considered a comparative effectiveness trial. The trial will be conducted in study centres in Europe, Australia and Canada. Study centres in countries of other continents may follow.

### Participant population

EAST-STROKE will randomise a minimum of 1746 patients with acute ischaemic stroke and AF. Inclusion and exclusion criteria are listed in Table 1. EAST-STROKE aims to achieve a balanced sex distribution in enrolment.

**Table 1 TB1:** Inclusion and exclusion criteria.

**Inclusion criteria** Acute ischaemic stroke confirmed by brain imaging or clinical diagnosis Randomisation within 4 weeks after stroke (patients are expected to be randomised as soon as possible after stroke, most often during initial hospitalisation for acute stroke treatment) AF first detected ≤ 1 year before randomisation (also paroxysmal AF) At least 1 ECG within recent 12 months that documents AF (documented current AF during index hospitalisation OR documented AF within the previous 12 months with sinus rhythm at the time of screening). The diagnosis of AF requires documentation by ECG. This will typically be a 6-lead or 12-lead ECG recorded in a medical practice or hospital. Documentation by consumer electronics (smart watches, apps or patient-operated ECG cards) is not sufficient as qualifying ECGs. Documentation on inpatient ECG-monitoring or a Holter ECG is acceptable as long as the requirements for AF duration outlined by current AF guidelines are met Age > 45 years Provision of written informed consent by the patient or—in case of incapacity of the patient—by a proxy according to national or local regulation **Exclusion criteria** *General exclusion criteria* End-stage cancer or life-expectancy < 12 months Participation in another clinical intervention trial, either within the past 2 months or ongoing Previous participation in the EAST-STROKE trial Pregnant women, women of childbearing potential not on adequate birth control (ie, highly effective methods of contraception with failure rate < 1%), breastfeeding women; for the purpose of this trial, a woman is considered of childbearing potential, ie, fertile, following menarche and until becoming post-menopausal unless permanently sterile (permanent sterilisation methods include hysterectomy, bilateral salpingectomy and bilateral oophorectomy; a post-menopausal state is defined as no menses for 12 months without an alternative medical cause; if a female participant cannot definitively attest to the absence of reproductive potential, a negative urine or serum ß-hCG test must be performed prior to recruitment) Drug abuse *Exclusion criteria related to acute ischaemic stroke* Severe stroke (ie, bedridden and fully dependent patients, mRS > 4) Any severe neurological complications after stroke that might impede the study results (eg, symptomatic ICH) *Exclusion criteria related to a cardiac condition* History of AF first diagnosed > 12 months prior to randomisation Patients not suitable for rhythm control of AF Prior AF ablation or surgical therapy for AF Severe mitral valve stenosis Prosthetic mitral valve Left atrial thrombi *Exclusion criteria based on laboratory abnormalities* Clinically relevant hepatic dysfunction requiring specific therapy Clinically manifest thyroid dysfunction requiring therapy. After successful treatment of thyroid dysfunction, patients may be enrolled when their thyroid function is controlled Severe renal impairment (stage IV or V; creatinine clearance < 30 mL/min, or requiring or almost requiring dialysis) *Exclusion criteria for specific investigational medicinal products* All contraindications listed in the summary of product characteristics (SmPC) of the specific investigational medicinal products considered for treatment in both treatment arms (intervention and comparator) apply and must be reviewed by the investigators prior to initiating any specific medical treatment

Abbreviations: AF, atrial fibrillation; EAST-STROKE, Early treatment of Atrial fibrillation for Stroke prevention Trial in acute STROKE; ECG: electrocardiogram; hCG, human chorionic gonadotropin; ICH, intracranial haemorrhage.

### Randomisation and blinding

Eligible patients will be randomised 1:1 to usual care (comparator) or usual care and early rhythm control (intervention). Randomisation will be stratified by country, age group (<70 years vs ≥70 years) and NIHSS score (<8 vs ≥8) using block randomisation with varying block sizes. Patients should be randomised as early as possible and must be randomised within 4 weeks of the index stroke onset date, preferably during hospitalisation.

Assessment of outcome events will be performed by assessors who are not aware of randomised group allocation. In addition, a blinded Endpoint Adjudication Committee will adjudicate all primary outcome events including all events that result in a hospitalisation.

### Treatment

EAST-STROKE is a comparative effectiveness trial that compares 2 treatment strategies in patients with acute ischaemic stroke and AF: usual care alone versus usual care and early rhythm control. All treatments (pharmacotherapy, cardioversion, ablation therapy) follow current standards and local practice with approved drugs and devices; no unapproved treatments are used. Individual treatment decisions, to achieve the randomised treatment aims, will be made by site teams.

The control arm follows standard AF management, which includes OAC, rate control and therapy of cardiovascular conditions in line with national and international guidelines. Anticoagulation therapy typically includes direct oral anticoagulants, vitamin K antagonists or other approved agents, eg, low-molecular-weight heparin, with initiation and monitoring following local protocols. Rate control, a primary approach in usual care, involves beta-blockers, calcium channel antagonists or digitalis glycosides. Dosing is adjusted to maintain a resting heart rate within a clinically acceptable range, typically below 100 or 110 beats per minute, with close monitoring for bradycardia or AF-related cardiomyopathy. Cardiovascular comorbidities will be managed according to standard practice without differences between randomised groups.^15^ Rhythm-control therapy in the usual care group follows local practice and is typically reserved for patients with persistent symptoms despite rate control.

Patients in the intervention arm will receive early rhythm control as soon as possible after randomisation. Rhythm-control therapy includes antiarrhythmic drugs (mainly amiodarone, dronedarone, flecainide, propafenone), cardioversion, ablation or any combination of these 3 approaches, following local practice. We expect that antiarrhythmic drugs will be the primary means of starting early rhythm-control therapy, selected based on safety and standard practice. For long-term rhythm control, antiarrhythmic drugs, AF ablation or both can be used. When performed, AF ablation aims at pulmonary vein isolation following standard recommendations. Patients randomised to early rhythm control should be initiated on antiarrhythmic drug therapy within 2 weeks after randomisation or undergo AF ablation within 8 weeks after randomisation. Patients unable to receive rhythm control safely within this period are not eligible. After randomisation, treatment continues as part of standard care, with follow-up conducted per protocol (Figure 1).

**Figure 1 f1:**
[figure not shown]
Trial schedule.

### Clinical evaluation and follow-up

Clinical evaluation at baseline will include collection of demographic data and information on medical history and medication, determination of pre-stroke functional status, recording of stroke characteristics (eg, time of symptom onset, location of stroke), physical examination, assessment of the neurological deficit using the NIHSS, assessment of the functional status using the mRS, assessment of cognitive function using the Montreal Cognitive Assessment (MoCA), vital parameters (ie, systolic and diastolic blood pressure, heart rate, body temperature), 12-lead ECG, standard laboratory parameters (ie, screening routine laboratory tests by the local laboratory), pregnancy test if applicable and transthoracic echocardiography (TTE).

The follow-up period comprises follow-up visits performed by telephone call, and 2 on-site follow-up visits (see Figure 1). Follow-up starts at 90 (±10) days after randomisation. Further follow-up visits will be scheduled at 6 (±1) months, 18 (±1) months, 30 (±1) months, and from then on every 6 (±1) months until the end of the trial. On-site follow-up visits will be scheduled 12 (±1) and 24 (±1) months after randomisation.

During follow-up via telephone patients will be asked for any events that may have occurred since the last follow-up visit, including outcome events and adverse events. Adherence to study treatment and concomitant medication will be recorded at each follow-up. The follow-up at 90 days will include assessment of quality of life using the EuroQol 5-dimensional questionnaire (EQ-5D-5L) and Patient-Reported Outcomes Measurement Information System-10 (PROMIS-10). On-site follow-up visits will be performed 12 (±1) and 24 (±1) months after randomisation and will comprise physical examination, assessment of the neurological deficit using the NIHSS, assessment of the functional status using the mRS, assessment of cognitive function using the MoCA, assessment of quality of life using the EQ-5D-5L and PROMIS-10, vital parameters, 12-lead ECG, information on other treatment for AF (ie, anticoagulation, rate control), assessment of outcome events, assessment of adverse events and recording of study treatments and concomitant medication. At 24 months, a TTE will be performed.

### Primary outcome

The primary outcome is a composite of first recurrent ischaemic stroke, haemorrhagic stroke, unclassified stroke, cardiovascular death or hospitalisation due to worsening of heart failure or due to acute coronary syndrome, analysed as time to the first occurrence of one of the aforementioned components. Definitions of outcome components follow definitions developed by the FDA and others for cardiovascular trials.^16^

### Secondary outcomes

Secondary outcomes are the individual components of the primary outcome, recurrent disabling stroke, recurrent AF, cardiac rhythm (sinus rhythm vs AF) at 12 and 24 months, unplanned cardiovascular hospitalisation, number of cardiovascular hospitalisations, change from baseline in left ventricular ejection fraction at 24 months, mRS at 12 and 24 months, quality of life assessed with the EQ-5D and PROMIS-10 global health including domains on physical and mental health at 12 and 24 months, cognitive function assessed with MoCA at 12 and 24 months and cost of therapy.

### Safety outcomes

Assessment of safety will comprise all-cause mortality and adverse events with a special focus on serious adverse events related to the study intervention with special emphasis on proarrhythmia and complications due to interventions, and severe bleeding complications, ie, ICH and major bleeding.

### Overall duration of the trial

EAST-STROKE is an event-driven trial, ie, the trial will be terminated after the calculated number of required primary outcomes have occurred. Based on the initial sample size calculation 351 events are required. Yet this number may be increased based on the sample size re-calculation at the interim analysis. A duration of the entire trial of around 5 years is expected. Enrolment is expected to last about 36 months. All patients will be followed-up until the end of the trial with a minimum follow-up period of 24 months and an expected mean follow-up period of 42 months.

### Data safety monitoring board (DSMB)

An independent data safety monitoring board (DSMB) is monitoring the trial. The DSMB will meet at least annually and after the interim analysis, which will be performed after 50% of the planned number of events have occurred. In addition, the DSMB will meet ad hoc whenever safety relevant data occur that might have an influence on the study.

### Sample size calculation

The sample size calculation is based on an adaptive design with one interim analysis (O’Brien and Fleming type α-spending function) including a sample size re-estimation after 50% of the planned number of events have occurred, with overall 1-sided significance level for superiority of 2.5% and power 90%. An event rate (cumulative incidence) at 2 years of 15% and 10.8% is assumed in the usual care and usual care + early rhythm control group, respectively, reflecting a treatment effect with an expected cause-specific hazard ratio of 0.7. In addition, competing risks are taken into account (with expected rate of competing events of 1% and 2% in the usual care and early rhythm-control therapy group, respectively, based on results of an EAST-AFNET 4 subgroup analysis^17^) as well as a loss-to-follow-up of 5% of the total observation time. Based on these assumptions, a total of 1746 (873 per group) patients are initially planned to be enrolled to observe the required number of 351 events. To avoid an unmanageably large sample size, the sample size after recalculation will be restricted to a maximum of 2620 patients (chosen based on practical reasons including feasibility of enrolment and a clinically meaningful effect). Under the same assumptions used in the presented sample size calculation, this sample size limit would allow to detect a hazard ratio of about 0.756 (or larger effects) with 90% power.

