### Interim analysis

After 176 events, ie, 50% of the planned events, an interim analysis with the possibility to stop for efficacy or futility will be conducted. The significance level for a stop for efficacy is determined by an O’Brien and Fleming type α-spending function at overall 1-sided significance level of 2.5%. For futility stopping, a non-binding boundary (*P* ≥ .5) is defined. The sample size re-calculation will be based on conditional power using the treatment effect derived by the interim analysis.^19^

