## Discussion

EAST-STROKE is an international, investigator-initiated, randomised controlled trial designed to assess the efficacy and safety of early rhythm control in patients with acute ischaemic stroke and AF. Despite the well-established role of OAC in preventing stroke in AF patients, the risk of recurrent stroke and major cardiovascular events remains substantial, even with optimal OAC. Given the high burden of AF-related strokes and their severe consequences, additional preventive strategies are needed.

Previous studies have suggested that maintaining sinus rhythm may offer further protection beyond OAC alone. However, prior rhythm-control trials focused on broader cardiology populations, and their applicability to acute stroke patients remains unclear. EAST-AFNET 4 demonstrated a significant reduction in cardiovascular events with early rhythm control in patients with recently diagnosed AF and cardiovascular comorbidities, but it did not specifically include patients with an acute ischaemic stroke.^9^ Subgroup analyses from EAST-AFNET 4,^17^ observational studies^11^ and a small pilot study^10^ indicate a potential benefit of rhythm control in stroke populations, supporting the hypothesis of EAST-STROKE. However, these findings require confirmation in a sufficiently powered trial.

EAST-STROKE will determine whether early rhythm control, in addition to usual care, reduces recurrent stroke and major cardiovascular events in patients with AF and acute ischaemic stroke. The trial incorporates a composite primary outcome, including recurrent ischaemic stroke, haemorrhagic stroke, unclassified stroke, cardiovascular death or hospitalisation due to heart failure or due to acute coronary syndrome, reflecting the broad spectrum of cardiovascular risks in this population.

EAST-STROKE is a therapy strategy trial delivering an innovative treatment concept, namely early rhythm control, using approved pharmacological and interventional therapies. The study’s adaptive design, including an interim analysis, permits an early stop for efficacy or futility. As part of the interim analysis, information from the current study population can be used to re-estimate the sample size more precisely, ensuring an adequate power.

Usual care in EAST-STROKE allows adaptation of acute stroke and AF management to new evidence emerging during the trial period in both study groups, thereby enhancing external validity and ensuring relevance to contemporary clinical practice.

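### The 90% power quoted at a hazard ratio of 0.756 is that of a design planned at 2620 patients from the start; the re-estimated design described in the article stays below 90% there

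*Protocol article*

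**What the plan says.** All places are in the protocol article.

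- *Sample size calculation*: "The sample size calculation is based on an adaptive design with one interim analysis", with an O'Brien-Fleming type spending function, one-sided 2.5% and 90% power. The initial plan is 1746 patients and 351 events. After re-estimation the number of patients is capped at 2620. On the same planning assumptions, "this sample size limit would allow to detect a hazard ratio of about 0.756 (or larger effects) with 90% power".
- *Statistical analysis*: the two stages are combined by the inverse normal method, each with weight √0.5.
- *Interim analysis*: the look takes place after 176 events, with efficacy stopping and a non-binding futility bound at P ≥ .5. "The sample size re-calculation will be based on conditional power using the treatment effect derived by the interim analysis". No conditional-power target is given.
- *Overall duration of the trial*: the trial ends on events, and the number required may rise after the interim. The cap itself is given in patients only.

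**The concern.** The 0.756 sentence closes a paragraph that opens with the adaptive design, and it supports the choice of the re-estimation cap. A reader will naturally take it as the sensitivity of this trial once re-estimation is allowed for.

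Three features of the described design work against that reading:

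- The look is at 176 events whatever the final size. That is half of 351, but only about a third of the events expected at the cap.
- The stage weights stay equal even if the second stage is twice as large as the first.
- The trial expands only when the interim estimate calls for it, so many trials finish well short of the cap.

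Each lowers power compared with a trial sized at 2620 from the outset. If the figure is read as the trial's own, the design is credited with slightly more sensitivity to moderate effects than it has.

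**Working it through.** **Inputs from the article.** "An event rate (cumulative incidence) at 2 years of 15% and 10.8% is assumed", "reflecting a treatment effect with an expected cause-specific hazard ratio of 0.7", and "expected rate of competing events of 1% and 2% in the usual care and early rhythm-control therapy group, respectively"; 5% of observation time lost; enrolment of 36 months; minimum follow-up of 24 months. I take the competing rates as 2-year figures and accrual as uniform, which matches the stated mean follow-up: 24 + 36/2 = 42 months.

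**Step 1. Boundaries.** O'Brien-Fleming type spending at 50% information gives c1 = 2.963 (one-sided p 0.00153) and c2 = 1.969. The drift for 90% power is 3.247.

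**Step 2. Reproduce the initial plan.** The annual total hazard is λ = −ln(1 − total 2-year incidence)/2, split in proportion to the incidences.

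- Usual care: λ = −ln(0.84)/2 = 0.0872; primary-event hazard 0.0872 × 15/16 = 0.0817.
- Early rhythm control: λ = −ln(0.872)/2 = 0.0685; primary-event hazard 0.0685 × 10.8/12.8 = 0.0578.
- Implied hazard ratio: 0.707.
- Events required: 4 × 3.247² / ln(0.707)² = 350.8. The article says 351.
- Probability of an observed primary event, with h the primary-event hazard: (h/λ) × [1 − (e^(−2λ) − e^(−5λ))/(3λ)] = 0.2446 and 0.1787.
- Events expected: 0.95 × 873 × (0.2446 + 0.1787) ≈ 351.

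**Step 3. Reproduce the 0.756.** Set the primary-event hazard under early rhythm control to 0.756 × 0.0817 and leave the competing hazard unchanged. The event probability becomes 0.1897.

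- Events expected in 2620 patients: 0.95 × 1310 × (0.2446 + 0.1897) ≈ 540.
- Events required at 0.756: 4 × 3.247² / ln(0.756)² = 539.
- Power with 540 events at 0.756: 90.1% fixed, 90.1% group-sequential with the look at half of 540, and 89.8% with futility followed.

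So 0.756 is the 90% point of a design planned at 2620 patients.

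**Step 4. Power of the described design at 0.756.** Let θ = −ln(0.756)/2 = 0.1399. The first-stage statistic Z1 has mean θ√176 = 1.855. If the trial continues, the second-stage statistic must exceed c(Z1) = (1.969 − √0.5·Z1)/√0.5. The second-stage events are D2 = 176 × [(c(Z1) + z_CP)/Z1]², where z_CP is the normal quantile of the conditional-power target. D2 is held between 351 − 176 = 175 and 540 − 176 = 364. Power is P(Z1 ≥ 2.963) plus the integral, over continued interims, of P(Z2 ≥ c(Z1)), where Z2 has mean θ√D2. Numerical integration gives the table below, and a simulation of 4 million trials agrees for targets of 80, 90 and 95%.

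| Assumed conditional-power target | Futility ignored | Futility followed |
|---|---|---|
| 80% | 85.3% | 84.3% |
| 90% | 86.5% | 85.5% |
| 95% | 87.3% | 86.3% |
| 99% | 88.4% | 87.3% |
| Always to the cap | 89.1% | 88.1% |

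The last row is an upper bound. At a true hazard ratio below 1, more second-stage events always raise the chance of rejection, so no rule held to 540 events can do better.

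Part of the loss comes from the equal weights. At the cap the combined statistic has the mean of a conventional analysis with (√176 + √364)²/2 ≈ 523 events, not 540. The rest comes from not expanding. With a 90% target and futility followed, 13% of trials stop for efficacy, 3% stop for futility, 29% stay at 351 events and 39% reach the cap. The expected number of events is 408.

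**Step 5. Where 90% is reached.** For targets of 80 to 95%, at a hazard ratio of 0.739 to 0.746 with futility ignored, and 0.736 to 0.743 with it followed. At 0.7 the same rules give about 96 to 97%.

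**Step 6. Sensitivity to the event yield.** With 527 (1.5 × 351) to 550 events at the cap, power at 0.756 is 83.8% to 87.8% for targets of 80 to 95%. It stays below 90% even if the trial always expands (at most 89.6%). With targets of 80 to 95%, reaching 90% at 0.756 would need a maximum of about 610 to 910 events.

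**The case against.** The strongest defence is that the sentence describes the limit, not the trial. Its subject is the sample size limit, its verb is conditional, and it applies the calculation that produced 1746 and 351 to the larger number. Read that way it is correct, and a reader who infers an arithmetic slip would be wrong. This part stands: the defect is in what the figure is attached to. It does not remove the point, because the paragraph bases its calculation on the adaptive design and gives no other power figure for the re-estimated trial.

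The second objection is that the size of the shortfall depends on a rule the article does not spell out. This also stands. A reader might take 84 to 87% as a property of the plan, but it holds only for assumed targets of 80 to 95%. A rule that keeps 351 events when interim conditional power is below 20 to 50% would give about 77 to 81%. The article may properly leave the target to the full protocol or analysis plan. The direction does not depend on it, since the upper bound is itself below 90%.

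Third, the practical effect is small: about 0.01 to 0.02 on a hazard ratio given as approximate. A null result would in any case be judged mainly by its confidence interval.

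A reader might also infer that the claim in the *Discussion* about "information from the current study population can be used to re-estimate the sample size more precisely, ensuring an adequate power" has to go. The numbers do not require that. At 0.756, re-estimation raises power from about 74% at 351 events to about 84 to 87%.

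**Conclusion.** The point holds as a mislabelled power figure. The 0.756 at 90% is right for a fixed or group-sequential design planned at 2620 patients and about 540 events. It is not the power of the design in *Statistical analysis* and *Interim analysis*, which at that hazard ratio is below 90% whatever the conditional-power target. The shortfall is at least about 1 to 2 points, and about 3 to 6 points under assumed targets of 80 to 95%.

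This rests on three assumptions: about 540 events at the cap under the stated accrual and follow-up, boundaries set at 50% information, and an event total held between 351 and the cap. The 84 to 87% and the 0.736 to 0.746 also rest on the assumed targets.

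A reader might go further and conclude that the trial is underpowered for its planned effect. The document does not support that: at 0.7 the re-estimated design has more than the planned 90%.

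**What to change.** In *Sample size calculation*, state that 0.756 is the reach of a design planned at 2620 patients from the start. Replace or supplement it with the sponsor's own simulated power for the actual re-estimation rule, giving the conditional-power target and the maximum number of events used. The figures above should not be copied in, because they rest on assumed targets.

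The cost is a short simulation, a sentence or two of text, and a stated sensitivity slightly less favourable than the present one. No change to the design or to the wording of the *Discussion* is required.
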